## **1. BACKGROUND**

Eleven National Sports Teams are located in the Quebec Metropolitan Area. In these groups, many athletes are aiming for Olympic medals in Beijing 2008 and Vancouver 2010 Olympic Games. A consultation of the coaches of these National Teams revealed that although a large proportion of these athletes present various cardio-respiratory symptoms, they do not have a rapid access to a systematic medical evaluation and follow-up. Furthermore, little is done in regard to prevention and optimization of treatment of pulmonary and cardiac conditions in the elite athlete's population of the Quebec area.

Cardiorespiratory problems are therefore commonly found in high-level athletes. However, these pathologies are not well characterized in athletes and the associated symptoms often not well perceived. These problems can be serious and it is important to detect them before they appear while setting up a systematic medical follow-up. Health professionals should monitor health of the young athletes and help to reduce the risks associated with high level exercise. The following project is an evaluation and follow-up program of high-level athletes, aiming at gathering key-information on long-term effects of high-level training on cardio-respiratory and metabolic parameters.

## **2. CARDIORESPIRATORY HEALTH OF ATHLETES**

Although musculo-skeletal injuries are undoubtedly the most frequent problems observed in high-level athletes, others such as asthma, cardiorespiratory disorders, chronic fatigue, exhaustion, recurring respiratory infections and metabolic disorders are also frequently encountered. Female athletes also have various specific health problems such as amenorrhea, osteoporosis and anorexia.

### **2.1 Respiratory problems**

Asthma is a complex disease which is the interaction between genetic and environmental factors. The prevalence of asthma has been increasing in the world in the last twenty years (particularly in children and young adults), which is about 5 to 10% in the general population. High-level athletes have the highest prevalence of asthma varying between 9 to 55%. Among the risk factors considered to contribute to the development of asthma are the hygiene hypothesis with a reduced exposure to microbial agents, allergy with particularly indoors exposure and pollutants, obesity and intense exercise.

#### **2.1.1 Exercise-induced asthma**

Exercise-induced asthma (EIA) is defined as an intermittent narrowing of the airways, generally occurring about 5 to 15 minutes after intense exercise. It is characterized by respiratory symptoms such as wheezing, dyspnea, chest tightness and cough. It is particularly high in winter sports athletes and in swimmers, and its prevalence has been reported to be increasing. Respiratory symptoms, associated or not with asthma, are frequently noted during training or competing periods and can interfere with the athlete's performance. The prevalence of exercise-induced

asthma has been reported to be high in female athlete. This effect of gender may be link with hormone or morphologic differences.

### **2.1.2 Treatment of asthma in athletes**

Furthermore, asthmatic athletes seem often refractory to current asthma medications, including the frequently used inhaled  $\beta_2$  agonist. This medication does not seem to have performance enhancing effects when used at dose required to prevent or treat exercise-induced bronchoconstriction, their use has been regulated. To ensure that  $\beta_2$  agonist are used in confirmed case of asthma, the International Olympics Committee-Medical Commission (IOC-MC) has established criteria for a positive diagnosis of asthma. This criteria include a significant bronchodilatator response, or a positive bronchial provocation challenge, that is a fall in FEV1 of at least 10% from pre-challenge measures being required for exercise or eucapnic voluntary hyperventilation. Accordingly, Dickinson *et al.* looked at the difference in the prevalence of asthma in the 2000 and 2004 British Olympic Team. A similar prevalence of asthma was found; 21.2% in 2000 and 20.7% in 2004. However, 7 athletes without previous diagnosis of asthma tested positive to the bronchoprovocation test and 21% previously diagnosed with asthma did not meet the IOC-MC criteria. This suggest that some athletes take an asthma medication without indication and expose them to sanctions, as inhaled corticosteroids and  $\beta_2$  agonists are on the prohibited substances list (World Anti-Doping Agency). Indeed, athletes need a medical exemption and tests to prove they really need these medications. Athletes and coaches may use  $\beta_2$  agonists to improve their physical performances, but studies demonstrated that this medication, inhaled at current doses, does not enhances performance in well trained non-asthmatic athletes.

Asthma in the athletes population is probably an heterogeneous entity and some athletes may have an asthma-like condition. Specific studies on the prevalence of asthma, airway hyperresponsiveness, exercise-induced bronchoconstriction, inflammatory states and mechanisms are needed. At this time, little is known about the effects of long term high level training on respiratory health. Therefore, not only do we need to know more on the long-term effects of training, but the optimal management of these problems in high-level athletes with or without asthma need to be the subject of a specific respiratory monitoring.

### **2.1.3 Exercise role in the development of asthma**

Exercise may induce a beneficial effect on the control of asthma when practiced at mild to moderate level in usual condition. However, it is possible that very intense and repeated exercise, particularly when performed over prolonged periods (years), could contribute to respiratory health problems such as recurrent upper respiratory track infection, rhinitis and asthma.

Helenius *et al.* showed that the risk of developing asthma was reported to be increased by 6 in endurance athletes and 3.5 in strength-speed athletes. A Norwegian epidemiologic study, also showed that the risk of developing asthma in elite athletes was higher than in the general population.

Indeed, high-level athletes have an increased prevalence of asthma, airway hyperresponsiveness and exercise-induced bronchoconstriction, and it has been suggested that intense and chronic training in various environments could lead or promote the development of airway diseases such as asthma. Weiler *et al.* showed that the prevalence of asthma was higher in Nagano Winter Olympics Games, with 22.4% compared to summer games with 16.7%. Athletes agreeing to complete a questionnaire, reported that they used medications for asthma, had a diagnosis of asthma, or both. The prevalence of asthma also seems to be higher for endurance sports, possibly

due to the high ventilatory demand required for prolonged time periods. The inhalation of large volumes of air to humidify and warm, may result in an osmotic and thermic stress on the airway. Hyperventilation can also cause a mechanical stress on the airway. Indeed, with a ventilation over 30L/min, most of the inhaled air is directly inhaled in the lung, bypassing the nose, and therefore the humidifying process. Dehydration may cause an osmotic stress and induce airway inflammation. This airway inflammation is associated with a vascular clogging and oedema and may be responsible of exercise-induced asthma.

#### **2.1.4 Cold air environment in athletes**

According to Freed *et al.* the dryness of cold air may be involved in the high prevalence of asthma-like symptoms reported by athletes who train in cold air. Many reports looked at the prevalence of those conditions in athletes exercising in cold air. Mannix *et al.*, found that 43 out of 124 skaters (35%) had a fall in FEV1 > 10% within the first minutes after the exercise routine. Leuppi *et al.* studied the prevalence of airway hyperresponsiveness (AHR) in athletes aged 17 to 35 years old and found a positive response to a methacholine challenge in 9 of 26 Swiss hockey players (35%) in comparison with 5 of 24 basketball players (21%,  $p < 0.05$ ), while the prevalence is estimated to be 7% in the Swiss population. Larsson *et al.* also showed that 33 of 42 (79%) elite cross-country skiers had an increased airway responsiveness, as defined by a fall of 20% in FEV1 and in asthma symptoms whereas only one of the control subjects had a comparable response.

### **2.1.5 Swimmers in indoor pools**

Previous studies showed that, among athletes training in various environments, swimmers have the highest prevalence of asthma. Indeed, Langdeau *et al.* showed that swimmers had the highest prevalence of bronchial hyperresponsiveness compared to others sports in different training environments. This higher prevalence is probably attributable to chlorine-derived compounds, the main disinfectants used in pools. Chlorine and organic matter interaction results in the formation of chloramines, such as monochloramines, dichloramines and nitrogen trichloride. This last is a volatile compound with powerful upper respiratory tract irritant properties. Lévesque *et al.* showed that symptoms associated with airway irritation during training were reported more frequently by young swimmers than by indoor soccer players. They also observed a link between the occurrence of these symptoms and chloramine concentrations, in the ambient air of indoor pools. This phenomenon is probably more marked in elite swimmers who train many hours a week at high intensity with high ventilation rate in this environment.

### **2.1.6 Swimmers in indoor pools**

**It has been previously shown that deep inspiration avoidance and time intervals between inhalation and measurement of FEV1 influence methacholine challenges in normal subjects but not in asthmatic nor in obese subjects. We would like first to verify if doing the eucapnic hyperventilation test before the methacholine challenge could influence the FEV1 fall after the methacholine. Secondly, we would like to verify if deep inspiration avoidance before inhalation could enhance the fall in FEV1 after the methacholine challenge, as previously reported.**

## **2.2 Cardiovascular problems**

In regard to cardiovascular disorders observed in athletes, the most common include hypertension, arrhythmia and congenital malformations. These pathologies, although less frequent, have serious consequences on athletes' health. They can be asymptomatic and they can be detected only by a systematic evaluation. A medical evaluation and an adequate long-term follow-up are necessary to detect these problems and to minimize their effects.

### 2.2.1 Cardiovascular effects of training

Trained endurance athletes have been noted to have profound bradycardia, which probably results from an increased cardiac vagal tone. Sacknoff *et al.* showed that chronic exercise affect heart rate variability. Heart rate variability is an index of cardiac autonomic modulation through the measurement of instantaneous beat-to-beat variations in R-R interval length. Low heart rate variability, which probably results from increased sympathetic modulation and diminished parasympathetic modulation has been associated with increased mortality after myocardial infarction. Long-term physical training may add to structural changes in athlete's heart distinct from normal subject. What is sometimes called *athlete's heart (AH)*, includes increased left-ventricular wall thickness and end-diastolic volume, sinus bradycardia at rest, a systolic murmur, audible third and fourth heart sounds, and cardiomegaly (heart weight generally > 500g) on chest radiograph. Electrocardiographic abnormalities may be seen in up to 40% of competitive athletes and likely result from electrophysiological changes remodeling associated with physical training. These changes are less common in female athletes. Increased cardiac mass is present in athletes who train isometrically (weight lifting) and isotonically (running, swimming). A study with professional cyclists, showed an increased in left atrial and ventricular dimension and ventricular wall after long-term isotonic exercise (approximately by 14% over controls).

### 2.2.2 Cardiac abnormalities in athletes

According to Burke *et al.* athletes under the age of 35 years are most likely to die of hypertrophic cardiomyopathy and coronary artery abnormalities. Hypertrophic cardiomyopathy is characterized by cardiomegaly, atrial dilation, small or normal size left ventricular cavity, asymmetric septal hypertrophy, and myofiber disarray within the septum, involving at least 5% of

muscle mass. Hypertrophic cardiopathy was the second most frequent cause of death (18%) and coronary artery atherosclerosis was the most frequent (30%). In a study by Maron *et al.* the most frequent cause of death was also hypertrophic cardiomyopathy (36%) and the second most frequent finding was aberrant coronary arteries (13%). Of note, 3% died from right ventricular dysplasia. Others causes of cardiac death during exercise include myocarditis, floppy mitral valve, aortic stenosis and dissections and sarcoidosis induced arrhythmias, but these conditions do not seem to be more prevalent in athletes. Idiopathic left ventricular hypertrophy represents a variant of hypertrophic cardiomyopathy, results from undiagnosed systemic hypertension, or represents a distinct form of idiopathic hypertrophy. Right ventricular dysplasia is a cardiomyopathy characterized clinically by abnormalities of conduction, repolarization and depolarization, and ventricular arrhythmias. For athletes older than 35 years, coronary atherosclerosis is the most common cause of cardiac sudden death (78%) and hypertrophic cardiomyopathy and right ventricular cardiomyopathy are uncommon (3% and 1%).

Young adults with symptoms such as palpitations, syncope, or ventricular tachycardia should be investigated by echocardiography, right contrast ventriculography, and programmed electrical stimulation studies. The most common coronary abnormality is a misplaced coronary ostium in which the left main and the right coronary artery arise from the sinus of Valsalva. There is strong evidence that this anomaly precipitates sudden death during exercise. As there is frequently an history of previous syncope, any child or young person who had evidences of cardiac ischemia or exercise-induced syncope should be investigated angiographically, mostly young elite athletes, because of the high-level exercise performed.

### **2.2.3 Sudden death in athletes**

The International Olympic Committee (IOC) stresses that the phenomenon of sudden death is underestimated in athletes. Cardiac lesions constitute the main cause of nontraumatic sudden death in high-level athletes. Two athletes out of 100 000 die each year of sudden death of cardiac origin compared to 0,7 person out of 100 000 in the general population. In 90% of cases, sudden death is primarily related to a preexistent cardiac abnormality. Other causes of sudden death, include asthma and other lung diseases, heath shock, cerebral embolism, sickle cell crisis, cerebral aneurysmal rupture, cranial traumatism, rachidian traumatism, doping and drug-addiction.

Most epidemiological studies have shown that persistent exercise is beneficial and prolongs life. Exercise may, however increase the risk of sudden death during or immediately after exertion in individual who have some cardiac conditions. It is therefore necessary to understand better what is predisposing athletes to sudden death.

The mechanisms of sudden death in athletes dying with hypertrophic cardiomyopathy include tachyarrhythmia arising in the malformed muscle mass or in ischemic areas of small vessel disease. The value of echocardiographic screening in asymptomatic young athletes is questionable, but it may distinguish with efficiency mild forms of hypertrophic cardiomyopathy from exercise-induced cardiac hypertrophy (athlete's heart). The value of a cardiac workup, including echocardiography, is indicated for athletes who have symptoms of syncope, arrhythmias or family history of sudden cardiac death. A genetic basis for familial hypertrophic cardiomyopathy has also been suggested in the form of a mutation of the gene coding for beta cardiac myosin heavy chain, located on chromosome 14q1. However, the clinical impact of these genetic findings in the athletes population needs to be investigated further.

**Table 1. Common cardiovascular causes of sudden death in athletes**

|                                                              |
|--------------------------------------------------------------|
| Cardiomyopathies                                      |
| Hypertrophic cardiomyopathy                                  |
| Arrhythmogenic right-ventricular dysplasia or cardiomyopathy |
| Dilated cardiomyopathy                                       |
| Idiopathic left-ventricular hypertrophy                      |
| Congenital malformation of coronary arteries          |
| Coronary artery aberrancies and abnormalities                |
| Intramural coronary artery (myocardial bridging)             |
| Coronary artery disease                               |
| Myocarditis                                           |
| Aortic rupture                                        |
| Marfan's syndrome                                            |
| Coarctation of aorta                                         |
| Valvular heart disease                                |
| Aortic stenosis                                              |
| Mitral valve stenosis                                        |
| Arrhythmias and conduction system abnormalities       |
| Long QT syndrome                                             |
| Wolf-Parkinson-White syndrome                                |
| Idiopathic ventricular tachycardia                           |
| Illicit drugs                                         |
| Anabolic steroids                                            |
| Human growth hormone                                         |
| Amphetamine                                                  |
| Ma Huang and ephedra alkaloids                               |
| Cocaine                                                      |

Modified from C.R. Vasamreddy *et al.* Clin Sports Med 23 (2004) 455-471

## **2.3 Metabolic problems**

Diet and exercise may increase body iron losses. Adequate iron stores are important to the athlete to provide adequate oxygen transport (haemoglobin), muscle aerobic metabolism (Krebs's cycle enzymes) and cognitive function. Inadequate calcium intake is also common in athletes, but sufficient dietary calcium is essential for normal bone growth, prevention and healing of stress fractures.

Exhaustive exercise generates excess of free radicals followed by increased lipid peroxidation and oxidative damages of other biomolecules. Prolonged high-grade oxidative stress caused damage

and it is recognized as playing an important role in the pathogenesis of several disorders, including cardiovascular disease. However, it has been suggested that regular adequate physical activity might maintain and promote the antioxidant defense capacity against oxidative stress. Recent findings have shown that high-sensitive C-reactive protein (hs-CRP), the inflammatory marker associated with higher risk of coronary heart disease, is decreased with regular physical exercise. However, there is not enough data indicating the effect of long-term intensive training on the oxidative stress status and the antioxidant defense capacity as well as on the hs-CRP level.

### **3. OBJECTIVES**

#### **3.1 General objectives**

- 3.1.1 Establish a long-term program of systematic evaluation and follow-up of cardiorespiratory health and performance of high elite athletes.
- 3.1.2 Evaluate the prevalence of respiratory, circulatory and metabolic problems among high-level athletes.
- 3.1.3 Evaluate the effects of treatments on cardiorespiratory conditions and exercise performance in athletes who need asthma medication.

#### **3.2 Specific objectives**

- 3.2.1 Determine seasonal and long-term changes in airway caliber, airway responsiveness to methacholine and inflammation in high-level athletes involved in long-term intense training.
- 3.2.2 Evaluate the perception of respiratory symptoms after various airway challenges and evaluate if there is discordance between subjective and objective assessment.
- 3.2.3 Assess the efficacy of asthma medications in asthmatic athletes.

3.2.4 Assess R-R variability in high-level athletes overtime.

3.2.5 Assess cardiac activity in high-level athletes.

3.2.6 Evaluate maximal aerobic capacity in high-level athletes.

**3.2.7. Evaluate the effect of deep inspiration avoidance and airway response to methacholine in athletes.**

## **4. HYPOTHESES**

4.1 Cardiorespiratory problems are frequent and often unrecognized in high-level athletes.

4.2 A systematic evaluation of cardiorespiratory function in athletes may improve their condition and sports performance in recognising undiagnosed cardiorespiratory problems who would benefit from.

4.3 Long-term intense training is associated with an increase in airway responsiveness, asthma, and structural change of heart (hypertrophy).

4.4 Response to asthma therapy is poor in asthmatic athletes, compared to non-athletes, suggesting different underlying pathophysiologic mechanisms.

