**4.5. Deep inspiration avoidance before methacholine inhalation enhances the fall of FEV1 in athletes.**

## **5. METHODS**

### **5.1 Study design**

Visits will be done by athletes to the laboratory on 2 occasions each year over a period of at least 3 years and field-tests at 2 times per year according to the annual planning schedule of each team, including 1 testing during competing season and 1 in the resting period. (For example, speed skaters begin their season in September and their resting period is in the month of April.) On the

first visit, consent form will be explained by the investigator or his/her delegate and signed by the subject. At the first visit, physical examination, medical questionnaire regarding their health condition, their family history of disease, their medication and their history in practicing their sport will be performed. Also, respiratory questionnaire, blood sample, eucapnic hyperventilation test, allergy prick skin test, methacholine challenge with Borg score and sputum analysis will be done, as well as the Holter. At the second visit maximal aerobic capacity test and MAPA will be done. At the third visit, spirometric field testing will be performed for each sports. Visit 4, 5 and 6 will be the same as visit 1, 2 and 3, except for allergy test which will be done only on the first visit.

| Visits                                 | 1 | 2 | 3 | 4 | 5 | 6 | 7 | 8 | 9 |
|----------------------------------------|---|---|---|---|---|---|---|---|---|
|                                        |   |   |   |   |   |   | X |   |   |
| Reading and signature of the assent    | X |   |   |   |   |   |   |   |   |
| Physical exam                          | X |   |   | X |   |   |   |   |   |
| Medical questionnaire                  | X |   |   | X |   |   |   |   |   |
| Anthropometric parameters              |   | X |   |   | X |   |   |   |   |
| VO2max test with ECG                   |   | X |   |   | X |   |   |   |   |
| Blood sample                           | X |   |   | X |   |   |   |   |   |
| Respiratory questionnaire              | X |   |   | X |   |   |   |   |   |
| Eucapnic hyperventilation test         | X |   |   | X |   |   |   |   |   |
| Allergy tests                          | X |   |   |   |   |   |   |   |   |
| Methacholine test + Borg score         | X |   |   | X |   |   | X | X | X |
| Induced sputum                         | X |   |   | X |   |   |   |   |   |

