## **4.5 Sample size**

As such study has never been done, we will recruited 100 subjects. There was no control group. Controls subjects will be include in under-studies.

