## **4.6 Analysis**

Descriptive statistics will be used to summarize the subjects' clinical characteristics. Normally distributed data will be reported as the arithmetic mean and standard deviation. Non-normally distributed data such as sputum cell count will be reported as the median and interquartile range. Non normally distributed data will undergo the most appropriate transformation to be normalised. A Wilcoxon signed rank test will be used to compare the data that could not be normalised. Significance will be accepted at a level of 95%. The analysis will be performed using the SPSS 10.0 statistical package (Chicago IL).

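### Hypothesis 4.2 cannot be answered by this design: no athlete in the main cohort goes unevaluated, and the two tabulated VO2max tests most plausibly fall in different training phases

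*Protocol*

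**What the plan says.** Section 4 (4.2) of the protocol states: "A systematic evaluation of cardiorespiratory function in athletes may improve their condition and sports performance", through recognition of problems not yet diagnosed. The evaluation is the cause, detection is the route, and condition and performance are the outcomes.

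Section 4.5 describes one group: "As such study has never been done, we will recruited 100 subjects". It adds "There was no control group", and then "Controls subjects will be include in under-studies". The sub-study controls are not defined further, and nothing says that they would be athletes who go without evaluation.

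Section 5.1 puts athletes in the laboratory twice a year for at least 3 years, with field tests also twice a year on each team's calendar, "including 1 testing during competing season and 1 in the resting period". On VO2max it says "At the second visit maximal aerobic capacity test and MAPA will be done", and visits 4 to 6 repeat visits 1 to 3 apart from the allergy test. The visit table accordingly marks VO2max at visits 2 and 5.

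Objective 3.2.6 on maximal aerobic capacity is descriptive. Section 4.6 gives descriptive statistics, a signed rank test for data that cannot be normalised, and "Significance will be accepted at a level of 95" per cent. Neither is tied to hypothesis 4.2.

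**The concern.** A hypothesis about the effect of being evaluated needs someone who was not evaluated, or at least a before-after contrast in which little else changes. The main cohort offers neither. Its only comparator is the athlete's own earlier round, and the next tabulated round most plausibly comes in a different part of the training year.

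At stake is what the study may conclude. Someone looking for evidence on 4.2 would naturally turn to the change in VO2max from visit 2 to visit 5. An ordinary difference in fitness between competition and rest could then be reported as benefit or harm from the programme. The other objectives (prevalence, seasonal airway change, perception of symptoms) do not depend on this.

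**Working it through.** **Inputs from the protocol.** n = 100 in a single group (4.5). Significance level 5%, sidedness not stated, so two-sided is assumed (4.6). VO2max at visits 2 and 5, two laboratory occasions a year, at least 3 years (5.1). The sample size of 100 cannot be reproduced, because no effect size, SD or power is given with it.

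**Which phase?** In 5.1 the season/rest clause follows directly after the field tests, so it could be read as covering those only. Objective 3.2.1, however, asks for seasonal change in methacholine responsiveness and inflammation. These are measured at laboratory visits 1 and 4, so those rounds need to differ in season. VO2max at visits 2 and 5 belongs to the same rounds. The broader reading is the more plausible one.

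**Can evaluation and phase be separated?** Write the expected result as a + b × phase + c × post, where post = 0 in the first round and 1 afterwards.

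- *Two tabulated tests, same phase order for all.* (phase, post) is (0, 0) and then (1, 1). The difference is b + c. There are three parameters and the rank is 2, so only the sum is estimable.
- *Six tests over 3 years.* Phase runs 0, 1, 0, 1, 0, 1 and post runs 0, 1, 1, 1, 1, 1. There are three parameters and the rank is 3. Round 3 minus round 1 gives c, free of phase.
- *Six tests plus a linear time trend d per year.* There are four parameters and the rank is 4. Round 3 minus round 1 is now c + d, and c is separated only by assuming the shape of the trend. Even then, c contains everything that changed after the first round: evaluation, treatment started, test familiarity and regression to the mean.

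**If phase order differs between teams.** Let p be the share of athletes whose first test is at rest, and b the season-minus-rest difference. The mean within-year change is c + (2p − 1) × b. With p = 0.5 the phase effect cancels. With p = 1 or p = 0 it enters in full, with opposite signs. The protocol does not fix p.

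**Size.** Let δ be the net phase shift in SDs of the within-athlete difference, with no evaluation effect. The documents give no value, so a range is assumed:

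P(significant) = 1 − Φ(1.96 − δ√100) + Φ(−1.96 − δ√100)

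| δ (assumed) | P(significant change) |
|---|---|
| 0 | 0.05 |
| 0.1 | 0.17 |
| 0.2 | 0.52 |
| 0.3 | 0.85 |
| 0.5 | >0.99 |

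The smallest change detectable with 80% power is (1.960 + 0.842)/√100 = 0.28 SD. A phase shift of that order would therefore usually be declared significant. With mixed order the shift shrinks by the factor (2p − 1): at p = 0.75, a shift of 0.2 SD becomes 0.1 SD and the probability falls from 0.52 to about 0.17.

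**The case against.** Several points on the other side are sound.

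- *There are more than two tests.* Two laboratory occasions a year for at least 3 years make at least six VO2max tests, three per phase. The table appears to show one annual cycle. A reader of the table alone might infer that VO2max is measured only twice; the text of 5.1 does not support that. This stands: the phase problem affects the within-year pair and can be avoided by same-phase comparison.
- *Confounding is not attribution.* A reader might infer that any gain or loss would be a training-phase effect. That does not follow. The cause of a change is unidentified, and phase is one candidate among several.
- *No visit 2 to visit 5 test is planned.* This stands as well. The protocol names no such test of 4.2, and analysis detail may properly sit in an SAP. But an SAP cannot create an unevaluated group, so the main difficulty remains.
- *Phase order may vary by team.* If so, aliasing across the cohort is partial, as shown above. The mean change then depends on a mix of calendars that nobody has set.
- *Hypothesis 4.2 says only that evaluation may improve matters.* It is indeed a hypothesis and not a claim, and it reads partly as rationale. It is still listed among the study's hypotheses, and this design cannot answer it.

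**Conclusion.** The point holds in a limited form. With every main-cohort athlete evaluated and no control group, an effect of evaluation on condition or performance is not identifiable, whatever analysis is chosen. This part rests on sections 4 and 4.5 alone and needs no assumption.

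The second part is conditional. If the season/rest clause covers the laboratory rounds, which objective 3.2.1 makes the more plausible reading, a within-year VO2max change cannot be distinguished from a phase effect unless phase order varies between teams. The false-positive probabilities of 0.17 to 0.85 for shifts of 0.1 to 0.3 SD illustrate the risk. They assume the shift, one phase order for everyone and complete pairs in all 100 athletes.

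Same-phase comparison across years removes the phase problem but not the lack of a comparator. Hypothesis 4.2 should be reworded; the remaining objectives are unaffected.

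**What to change.** Restate 4.2 as what the design can show: the number and proportion of athletes found to have a previously unrecognised cardiorespiratory condition, and the proportion whose management changed as a result. This sits close to hypothesis 4.1 and objective 3.1.2; the follow-through on management is the new element.

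If a performance change is reported, add one analysis sentence: compare VO2max only between tests in the same training phase of successive years, label the result exploratory, and do not attribute it to the programme.

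Contrasting athletes who had a finding acted upon with those who had none would not repair the hypothesis. It compares affected with unaffected athletes, is open to regression to the mean, and still includes nobody unevaluated.

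While the text is open, section 5.1 could say whether the season/rest clause covers the laboratory visits and mark the table as one annual cycle.

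The cost is a more modest claim, the recording of management changes at follow-up visits, and a performance comparison that waits for a second same-phase test. That test falls within the stated follow-up, so no visit or test is added.
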